#### Variables of interest study 1A and 1B

For clarity, the variables of interest are reported here for the effectiveness study (1A) and the economic evaluation (1B) separately. Demographic and descriptive variables are relevant for both studies 1A and 1B.

**Demographic and Descriptive Variables.** Basic demographics (gender, age, nationality, level of education, employment status, housing), and SMI-specific variables (mental health problems; self-reported and officially diagnosed, duration of mental health problems, health care use) will be used to describe the sample. As noted, many of these variables will be used to match participants from the control group (panel members) with participants from the experimental group (RC students). Furthermore, participants in the experimental group will indicate in what way and how frequently they are active at the RC.

#### Variables of interest for study 1A: effectiveness

**Primary Outcome Measure: Empowerment.** The main dependent variable, empowerment, will be operationalized by the Netherlands Empowerment List (NEL; [49]). Originally, the NEL consists of six subscales (social support, professional help, connectedness, confidence and purpose, self-management and caring community). To keep the survey length manageable, we have selected three subscales as an operationalization of personal empowerment, following Boevink, Kroon [49]: confidence and purpose, connectedness and self-management. This selection “describes feelings, competencies and actions reflective of personal empowerment” [49]. The NEL has shown good internal consistency (Cronbach α = 0.94), aspects of validity, reproducibility (Cronbach α = 0.79), and responsiveness [49, 50]^4^. Example items are “I think of myself as a person worth something” (confidence and purpose), “I regularly meet people outside my home” (connectedness), and “I am able to set my boundaries” (self-management). Items are answered on a 5-point Likert scale (‘1’ = Strongly disagree, ‘5’ = Strongly agree).

**Secondary Outcome Measures.** This study investigates five secondary outcomes.

***Quality of Life.*** To measure quality of life the 8-item Maastricht QoL Scale [51] will be used. Participants rate their satisfaction about their living situation, social contacts, daily activities, financial situation, mental health, physical health, received care, and their life as a whole. An example item is “How satisfied are you with your daily activities?”. Items are answered on a 7-point Likert scale (‘1’ = Not at all satisfied, ‘7’ = Extremely satisfied).

***Mental Health.*** To measure mental health, the MHI-5 [52] will be used. Five items inquire about the frequency of experiencing negative and positive affect, anxiety and depression during the past four weeks. An example item is “How much of the time, during the last four weeks, have you felt calm and peaceful?”. Items are answered on a 6-point Likert scale (‘1’ = Constantly, ‘6’ = Never).

***Loneliness***. Loneliness can be defined as a state of mind where one is unsatisfied with the quantity and quality of their social network [53]. The 11-item DeJong Gierveld Loneliness Scale [54] will be used to operationalize loneliness. This scale is comprised of two subscales measuring emotional loneliness (6 items) and social loneliness (5 items; [55]). Example items are “I miss having a really close friend” (emotional loneliness), and “I miss having people around me” (social loneliness). Items are answered on a 5-point scale (‘1’ = Yes!, ‘2’ = Yes, ‘3’ = More or less, ‘4’ = No, ‘5’ = No!).

***Satisfaction with Care and Support.*** To measure how satisfied participants are with received care and support, we will use an adapted inventory from Menting [56]. Originally this inventory is targeted at people with chronic illness, so we adapted the items to concern mental health care specifically. Participants provide a rating for specific health care providers (e.g., general practitioner, psychiatrist) ranging from 1 to 10, with a higher score representing a higher satisfaction with received care and support. Participants only provide a rating for specific health care providers of whom they have received care in the past 12 months. In addition to these ratings from the adapted inventory [56], participants also rate their general satisfaction with received care and support from care providers and their social network. These two items are answered on a 5-point Likert scale (‘1’ = Very unsatisfied, ‘5’ = Very satisfied). Finally, we added two items inquiring the extent to which the received care and support from care providers and their social network matches participants’ needs, on a scale from 1 to 10 (‘1’ = Extremely bad, ‘10’ = Excellent).

***Self-Stigma***. Self-stigma, or internalized stigma, refers to the application of negative stereotypes and discrimination to oneself, and will be operationalized by the 10-item Internalized Stigma of Mental Illness scale (ISMI-10; [57]). An example item is “Mentally ill people tend to be violent”. Items are answered on a 4-point Likert scale (‘1’ = Strongly disagree, ‘4’ = Strongly agree).

#### Variables of interest study 1B: economic evaluation

***Resource Use.*** To assess (informal) care use of participants, the Trimbos and iMTA questionnaire on Costs associated with Psychiatric illness (TiC-P; [58]) will be used, with a recall period of three months. This includes questions on medication and contact-hours with care providers but also questions about informal care received from one’s own social network (e.g., family, acquaintances, neighbours). To assess community outcomes such as employment, again the TiC-P [58] will be used. This includes questions on whether participants have employment or are active as volunteer, absenteeism and presenteeism of their (un)paid jobs. The recall period for absenteeism and presenteeism is four weeks. Housing status (e.g., living independently, living in a hospital/sheltered or supported housing residence, having no permanent residence) will also be determined by one item that we formulated (not in the TiC-P).

***Quality-Adjusted Life Years.*** In line with the Dutch guidelines for economic evaluations, quality-adjusted life years (i.e., QALYs) will be computed using utilities derived from the EuroQol-5-dimensions-5-level-questionaire (EQ-5D-5 L; [59]). The EQ-5D-5 L consists of six items, of which five inquire about specific restrictions in daily life (i.e., health states), with regards to mobility, self-care, usual activities, pain/discomfort and anxiety/depression. Possible answers on these items range from 1 to 5, where ‘1’ = Indicating no problem and ‘5’ = Indicating unable to/extreme problems. One final item regards the general health state (the EQ VAS: “We would like to know how good or bad your health is TODAY. Mark an X on the scale to indicate how your health is TODAY”). This general health state is represented by a number between 0 and 100, where ‘0’ = The worst health you can imagine, and ‘100’ = The best health you can imagine. The health states from the EQ-5D-5 L will be computed into utilities using the Dutch tariffs of EuroQol [60]. By means of the area under the curve method, time periods between assessment waves will be weighted by these utilities, which results in QALYs adjusted over the timeframe of 24 months. An overview of all measures can be found in Table 1.

**Table 1 Tab1:** Overview of all variables of interest and its matching instruments as used in Study 1

Measurement level	Variable of interest	Instrument	Reference
Primary	Empowerment	NEL	Boevink, Kroon (49)
Secondary	Quality of life	Maastricht QoL	Drukker, Bak (51)
	Mental health	MHI-5 (from RAND-36)	Berwick, Murphy (52)
	Loneliness	DeJong Gierveld Loneliness Scale	de Jong-Gierveld and Van Tilburg (54)
	Satisfaction with care and support	Adapted inventory	Menting (56)
	Self-stigma	ISMI-10	Boyd, Otilingam and DeForge (57)
Economic evaluation	Resource use	TiC-P	Hakkaart-Van Roijen (58)
	Quality-adjusted life years	EQ-5D-5 L	Rabin and Charro (59)

*Note*. All measures are self-reported

#### Sample size

The required sample size to reach at least 80% power is determined through simulation using the R packages simstudy [61] and faux [62]. To our knowledge, no previous studies included empowerment as primary outcome variable, so our estimation of the expected effect size of Cohen’s D is based on previous work on peer support effectiveness [63] and on RC effectiveness [20]. These effect sizes were small. In our case, the hybrid nature of RC attendance and the selection of NEL subscales may potentially lower the capability to detect clinically relevant changes^5^. On the other hand, the NEL has proven to be sensitive to change in recovery-oriented practices (e.g., medium effect size in Tjaden, Mulder [64] after 18 months). All this considered, we assume an effect size of Cohen’s D = 0.3. Assuming Cohen’s D = 0.3, a Pearson’s correlation coefficient of 0.6 between subsequent measurements [64] and 30% dropout at t_4_ we expect to detect a significant difference in 82.8% of the time between the control and experimental group when a total 250 participants are to be included. Participants for the control group will be recruited from the existing panel through propensity score matching, hence the study is appropriately powered when 125 participants for the experimental group have been included and matched to 125 control participants.

#### Analyses

In our primary (cost-)effectiveness analyses we will adopt an intention-to-treat approach. Since RCs attendance is voluntary, RCs are available-to-all and are increasingly implemented in the Netherlands, we are aware that cross-overs during the study’s timeframe are likely to occur (e.g., individuals who were active RC students at t_0_ but not anymore at t_3_, or vice versa). However, given the pragmatic nature of the study, we will not take cross-overs into account and treat participants according to their original condition. Depending on the number of actual cross-overs we might explore their impact in a sensitivity analysis. Another sensitivity analysis will concern the nature of RC attendance. Given the hybrid nature of RC attendance in the Netherlands (e.g., one can follow courses, visit the social meeting ground, volunteer) we will compare effects of RC attendance in the broad sense with effects of RC attendance for students who participate in courses (more in line with international literature). Potential baseline between-group differences that were not accounted for in the matching procedure will be checked and controlled for if needed. We will adopt single imputation nested in bootstrapping to deal with missing values and skewed data [65]. All analyses will be conducted in SPSS version 29 + and/or R version 4.2+. In the following sections, the specific analyses to examine the effectiveness and economic evaluation of RCs are described separately.

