#### Design

Random allocation to conditions is not feasible, since that would counteract the open-to-all accessibility of RCs. To allow for drawing reliable and valid conclusions, we will adopt a quasi-experimental design where RC students (the experimental group) are compared with members of the Dutch panel of people with severe mental illness (i.e., SMI) (the control group), based on propensity score matching. The Dutch panel of people with SMI (hereafter referred to as ‘the panel’) is a national panel with over 1,500 members who have lived experience with mental vulnerabilities. The target group of this panel is specified as “people (aged ≥ 18) experiencing various SMI” and is expected to be similar to the target group of RCs (for more detailed information on the panel, see de Lange, Michon [45]). RC students receive the same questionnaires as members of the panel (i.e., the control group). All participants (in both the experimental and control group) will fill out a survey every six months, for a two-year period (5 assessments in total). To minimize recall bias (e.g., when determining resource use; [46, 47]) and to determine cumulative quality-adjusted life years, outcomes relevant for the economic evaluation were included in all five waves. Relevant measures to determine the effectiveness of RCs will only be included in t_0_, t_2_ and t_4_ to keep the survey length manageable (every year; see Fig. 1).

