Variables that will be used for the matching are gender, age, nationality, level of education and diagnoses (psychotic disorders, mood disorders, anxiety disorders, personality disorders, substance use disorders, neurodevelopmental disorders, eating disorders). If someone does not have an official diagnosis, we will use self-reported diagnosis as a proxy. Although potentially relevant, duration of service use will not be used as matching variable since true baseline data are unavailable; the experimental group may be already active at the RC for a significant amount of time at t_0,_ which may have impacted service use. Each participant from the experimental group will be matched to one or more participants from the control group. Given the large sample size of the control group and the limited number of matching variables, we will likely retrieve multiple good matches per RC partaker, reducing uncertainties and increasing reliability.

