#### Analysis study 1B: economic evaluation

The economic evaluation will constitute both a cost-effectiveness analysis (CEA) and a cost-utility analysis (CUA). In line with the Dutch guidelines, a societal perspective will be adopted indicating that all costs should be included, regardless of who carries these costs [69]. Hence, four types of costs will be included (all expressed in Euros), namely (1) intervention costs, (2) patient and family out of pocket costs, (3) mental health care services costs and (4) costs due to productivity loss. Intervention costs will be estimated with input from experts coordinating RCs. Patient and family out of pocket costs refer to costs from help and support provided by the informal network of someone [70]. To determine costs the most recent costing manual will be used (at the time of writing this is [70]), with applied indexation if needed. Finally, costs of productivity loss include costs of absenteeism and presenteeism (i.e., being present at work but less efficient) of paid employment and volunteer jobs and will be determined by means of the friction cost method [71]. Since our data collection covers a time period of two years, costs will be indexed to the starting year 2022.

For the CEA, the primary outcome will be a proportion of responders based on the NEL after 24 months, which refers to whether or not participants (both experimental and control group) show a significant difference in self-reported empowerment at t_4_ as compared to t_0_. This variable will be dichotomized using the reliable change index by Jacobson and Truax [72]. For the CUA, the primary outcome will be the total incremental QALYs during the study’s timeframe of 24 months. Cumulative costs will be calculated based on this same time period.

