To determine the cost-effectiveness of RC attendance, incremental cost-effectiveness ratios (ICERs) will be calculated for both the CEA and CUA, following Drummond, Sculpher [73]: ICER = (Costs^RC^ – Costs^control^)/(Effects^RC^ – Effects^control^). These ICERS are representative of average incremental costs associated with one additional unit of the measure of effect. Thus, the ICERs of the CEA represent the incremental costs per significant change in self-reported empowerment, and the ICERs of the CUA refer to incremental costs per QALY gained. Analysis will be done according to the intention-to-treat principle. We will use single imputations nested in non-parametric bootstrapping (N > 2500 bootstrapped samples) combined with seemingly unrelated regression equations [65]. Next, incremental costs, incremental effects and ICERS will be calculated. Sensitivity analyses will be conducted to assess the robustness of the findings, for example by running an analysis from the health care perspective (excl. patient and family costs, informal costs and productivity losses) [73].

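### The cost-utility analysis does not commit to adjusting for t0 utility and t0 cost; in a non-randomised comparison, adjustment is left to an undefined baseline check

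*Protocol article*

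**What the plan says.** The Design section rules out randomisation: "Random allocation to conditions is not feasible, since that would counteract the open-to-all accessibility of RCs". RC students are compared with matched members of a national panel.

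The Matching paragraph under Procedures says "Variables that will be used for the matching are gender, age, nationality, level of education and diagnoses", followed by a list of diagnostic groups. EQ-5D-5L utility, costs and service use are not among them. Duration of service use is left out on purpose, because "the experimental group may be already active at the RC for a significant amount of time at" t0 and service use may already have been affected.

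On the construction of QALYs, the section on variables for Study 1B says: "By means of the area under the curve method, time periods between assessment waves will be weighted by these utilities". The analysis section for Study 1B then states: "For the CUA, the primary outcome will be the total incremental QALYs" over 24 months, with costs accumulated over the same period. The ICER is the difference in costs divided by the difference in effects. Estimation uses single imputation nested in a bootstrap, "combined with seemingly unrelated regression equations". No covariate is named for either equation.

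The general Analyses section, which covers both Study 1A and Study 1B, contains the only adjustment rule: "Potential baseline between-group differences that were not accounted for in the matching procedure will be checked and controlled for if needed".

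**The concern.** Matching on demographics and diagnoses does not balance utility or cost at t0 by design. An area-under-the-curve QALY includes the t0 utility itself and every later utility that still reflects it. Cumulative cost likewise contains whatever part of a t0 cost gap continues into follow-up. If neither t0 value is in the model, such a gap is reported as QALYs or euros attributable to RC attendance.

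The other analyses handle this differently. The Study 1A model has a separate group term, so its effect is read from the group-by-time interaction. The responder outcome of the cost-effectiveness analysis (CEA) compares each participant's t4 score with that participant's own t0 score. The total QALY of the cost-utility analysis (CUA) has no such reference. The evaluations may therefore answer different questions within one paper.

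The adjustment rule is also data-dependent. It names no variables, no measure of imbalance and no threshold, so the choice between an adjusted and an unadjusted ICER can be made after the data are seen.

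**Working it through.** The plan gives no figure for a t0 utility or cost gap, for its persistence, for the QALY difference or for the ICER. There is nothing to reproduce, and the size below is an illustration on stated assumptions.

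**Weights (from the Design section).** Five waves at 0, 6, 12, 18 and 24 months give trapezoid weights in years of 0.25, 0.5, 0.5, 0.5 and 0.25, which sum to 2.0.

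**Spurious QALY difference.** Assume no RC effect and a t0 utility gap d between groups. If the share of the gap remaining at wave k is p_k (with p_0 = 1), the spurious difference is d × Σ w_k p_k.

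- Gap at t0 only: 0.25 d.
- Decay by a factor 0.6 per wave: 0.25 + 0.5 × (0.6 + 0.36 + 0.216) + 0.25 × 0.1296 = 0.870, so 0.87 d.
- Constant share of 0.6 at t1 to t4: 0.25 + 1.75 × 0.6 = 1.30, so 1.30 d.
- Constant share of 0.8: 0.25 + 1.75 × 0.8 = 1.65, so 1.65 d.
- Fully persistent: 2.00 d.

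| Persistence (assumed) | d = 0.02 | d = 0.05 | d = 0.10 |
|---|---|---|---|
| t0 only | 0.005 | 0.0125 | 0.025 |
| decay 0.6 per wave | 0.017 | 0.044 | 0.087 |
| constant 0.6 | 0.026 | 0.065 | 0.130 |
| constant 0.8 | 0.033 | 0.083 | 0.165 |
| full | 0.040 | 0.100 | 0.200 |

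The value 0.6 is borrowed from the Sample size section, where it is a correlation between successive empowerment scores. A correlation between persons is not the persistence of a difference in group means, so it serves only as a convenient point in the range.

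**Costs.** Twenty-four months hold eight three-month periods. A gap of C euros per three months that persists throughout adds 8 × C. With C = 500 this is 4,000 euros.

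**Effect on the ICER (all inputs assumed).** Take a true gain of 0.05 QALY and a true extra cost of 1,000 euros: 1,000 / 0.05 = 20,000 per QALY. With a fully persistent utility gap:

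- +0.05: 1,000 / (0.05 + 0.10) ≈ 6,700.
- +0.02: 1,000 / (0.05 + 0.04) ≈ 11,100.
- −0.02: 1,000 / (0.05 − 0.04) = 100,000.
- −0.05: the QALY difference becomes 0.05 − 0.10 = −0.05, so its sign reverses.

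A cost gap of 500 euros per three months with no utility gap gives (1,000 + 4,000) / 0.05 = 100,000.

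**If the check were a significance test.** The plan does not say that it is. With 125 per group, the standard error of the t0 utility difference is SD × √(2/125). For assumed SDs of 0.20, 0.25 and 0.30 this is 0.025, 0.032 and 0.038, and two-sided 5% power to detect a gap of 0.05 is 51%, 35% and 26%. Such a test would miss that gap about half the time or more.

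**The case against.** The strongest reply is that a reader might infer that the plan compares raw QALYs and costs, and the document does not say so. Seemingly unrelated regression can carry covariates, and the conditional adjustment clause applies to the economic analyses. An unadjusted comparison is permitted, not prescribed. That stands.

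It can also be said that the covariates of each equation belong in an analysis plan that is not shown. Had the article been silent, this would settle the matter. But the article states a rule, and that rule makes adjustment depend on an undefined look at the data.

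Three further readings go beyond the text:

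- A reader might take the check to be a p-value. The plan names no test; it could mean standardised differences or a judgement of relevance. The power figures apply only under the first reading.
- A reader might conclude that t0 costs are themselves counted in the 24-month total. The cost questionnaire recalls three months, so the t0 answers describe time before t0, and the plan does not say that they are included. Only a gap that persists is certain to matter.
- A reader might think that only the CUA is affected. The CEA uses the same cumulative costs, and the chance of a reliable change can still depend on the t0 score.

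The weightiest objection concerns the remedy. The Matching paragraph says that true baseline data are unavailable because RC students may already have been attending. Conditioning on t0 utility and t0 cost may remove part of an effect already achieved. This is a real cost of adjustment. It does not favour leaving the choice open, since the plan's other analyses already measure from t0.

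**Conclusion.** The point holds in this form: the plan does not commit to t0 utility and t0 cost as covariates in the regressions behind the ICER, and the rule it gives instead has no variables and no criterion. In a non-randomised comparison that leaves both quantities unmatched, a persisting t0 gap can pass into incremental QALYs and costs. This should be corrected before analysis.

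The size depends wholly on assumptions. For a gap of 0.05 and no RC effect, the spurious difference runs from 0.0125 to 0.10 QALY, according to persistence. A reader might infer that imbalance will decide the sign of the ICER. The documents do not support that: they give neither the size nor the direction of any gap, and the sign reversal above needs a fully persistent gap of −0.05 against an assumed gain of 0.05.

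**What to change.** State in the Study 1B analysis section that the QALY equation always includes t0 EQ-5D-5L utility and the cost equation always includes t0 cost, each with the matching variables, whatever a baseline check shows. Report the ICER without t0 adjustment as a sensitivity analysis.

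Add one sentence on interpretation: because RC students may already be active at t0, their t0 utility and cost may partly reflect earlier attendance. The adjusted ICER therefore estimates the effect of attendance from t0 onward, not of RC attendance as a whole.

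The cost is a few sentences and two covariates. The Design section places the economic measures in all five waves, so no new data are needed. What is given up is any claim that the main ICER captures benefit or savings gained before t0; the sensitivity analysis shows how much the adjustment changes.
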